## **2.14 Data Management**

### **2.14.1 Data collection and storage**

Data will be collected through interviewing the patients, from their medical files/treatment charts and source data documents and will be recorded on the CRF. The CRFs will be checked for completeness and accuracy against the source data. Original CRFs will be used when entering information into the computer database. The database will be checked against the CRFs for accuracy. Data analysis will begin after ensuring that all the data have been accurately entered.

Data will be kept in a password secured computer to ensure confidentiality and all the blood samples and documents during the study period will be stored by the investigator until time for destruction after the data have been analyzed and published.

## **2.15 Ethical considerations and approval**

### **2.15.1 Ethical issues**

The main aspect of this trial that raises ethical issues is the fact that it is necessary to collect samples for HIV-related laboratory testing. During follow up the patients may be asked to share information about their wellbeing and some of the information may be viewed by them as sensitive. Subject confidentiality will therefore be strictly held in trust by the participating investigators and the research staff. This confidentiality will be extended to cover testing of biological samples in addition to the clinical information relating to participating subjects. The study protocol, documentation, data and all other information generated will be held in strict confidence. No information concerning the study or the data will be released to any unauthorized third party, without prior written approval. All laboratory specimens, evaluation forms, reports and other records that will leave the site will be identified only by the subject study number to maintain subject confidentiality. Clinical information will not be released without written permission of the subject, except as necessary for monitoring by the ethical committees.

If bleeding occurs, study drug will be stopped and immediate clinical assessment will be undertaken and the participant will be managed accordingly.

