#### **2.8.1.3 Dose modification**

There will be no any allowable dose modifications.

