#### **2.9.2.2 Exclusion Criteria**

Patients meeting any of the following criteria will be excluded from the study:

- Previous intolerance or allergy to ASA or any ASA products
- Asthmatics
- Predisposition to bleeding
- Antithrombotic therapy
- Therapy with prohibited drugs (see appendix 5)
- Active or history of peptic ulcer disease
- Pregnancy
- Severe renal disease (eGFR <30 ml/min/1.73 m^2)

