#### **2.9.6 Subject Withdrawal**

##### **2.9.6.1 Reasons for withdrawal**

The investigator may withdraw a patient from the study treatment procedures if the patient;

- Will be in violation of the protocol and/or
- Will experience an SAE that is related to the study drug and/or
- Will develop, during the course of the study, symptoms or conditions listed in the exclusion criteria and/or

- Will require a medication that is prohibited by the protocol

The investigator will also withdraw all participants from the study treatment if the study is terminated. Patients will be free to withdraw from the study at any time upon their request.

All the patients who will be withdrawn from the study will be followed up to completion of six months of follow up.

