### **2.15.2 Ethical approval**

The study will be conducted according to ICH GCP guidelines and the Declaration of Helsinki (Version 2008), and it is the responsibility of the Investigators to ensure adherence. The investigator will ensure all personnel involved in the study are already trained for Good Clinical Practice (GCP) and/or Good Clinical and Laboratory Practice (GCLP). Study personnel will also be trained on standard operating procedures (SOPs) that are related to the protocol and will follow the GCP and GCLP guidelines.

Patients who will present with SAE that will be related to the study drugs will be stopped from taking the study drugs and referred to the study clinician for management. These patients will then be followed up to complete the 12 months of follow up.

This protocol will be submitted concurrently to the institutional ethical committees of the Muhimbili University of Health and Allied Sciences (MUHAS) and the National Health Research Ethics Committee at the National Institute of Medical Research (NIMR) for ethical approval. Letters of protocol approval by the ethical committees will have to be obtained prior to the commencement of the study, as well as approval for other study documents subject to ethical committees' review. Approval of the protocol and the study drugs will be done by the Tanzania Medicine and Medical Devices Authority (TMDA).

The Investigator and the Supervisors will also be responsible for informing the ethics committees of any SAEs as required, and submitting six monthly report as required. No study materials will be obtained from study participants before approval from the relevant bodies.

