| 1.        | Does the participant have history of intolerance or allergy to ASA or any ASA containing products or NSAIDs or celecoxib or other salicylates or sulphonamides? |          |    |
| 2.        | Is the participant asthmatic?                                                                                                                                   |          |    |
| 3.        | Does the participant have any bleeding diatheses?                                                                                                               |          |    |
| 4.        | Does the participant have active or history of peptic ulceration or gastrointestinal bleeding within the last year?                                             |          |    |
| 5.        | Is the participant on antithrombotic/ antiplatelet therapy?                                                                                                     |          |    |
| 6.        | Is the participant on current or previous regular use of ASA at any dose or current use of another NSAID?                                                       |          |    |
| 7.        | Is the participant on current or long term use of oral corticosteroids?                                                                                         |          |    |
| 8.        | Is the participant's urine pregnancy test positive?                                                                                                             |          |    |
| 9.        | Does the participant have history of moderate or severe renal impairment, with eGFR < 45 ml/ min/ 1.73 m                                            |          |    |

VI: SELECTION OF PARTICIPANTS INTO THE TRIAL

1. Is the participant eligible? \_\_\_\_ (YES/NO) If no why? \_\_\_\_\_
2. Is the participant selected into the study? \_\_\_\_ (YES/NO) If no why?  
\_\_\_\_\_
3. Participant's study number \_\_\_\_\_
4. Investigator's signature \_\_\_\_\_ Date \_\_\_\_/\_\_\_\_/\_\_\_\_

**BASELINE INFORMATION FORM AFTER SELECTION INTO THE STUDY** (*To be filled in on Visit 0*)

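### The rules for stopping study drug in an individual patient are not aligned: a drug-related SAE is a mandatory stop in one section and discretionary in another, and the withdrawal list does not name bleeding

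*Protocol*

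**What the plan says.** Three sections of the protocol govern stopping study drug in an individual patient.

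- **Section 2.9.6.1 (Reasons for withdrawal)** opens with "The investigator may withdraw a patient from the study treatment procedures if the patient" and then gives four reasons: violation of the protocol, an SAE related to study drug ("Will experience an SAE that is related to the study drug and/or"), an exclusion condition arising on study ("Will develop, during the course of the study, symptoms or conditions listed in the exclusion criteria"), and need for a prohibited medication. The opening verb applies to all four.
- **Section 2.15.2 (Ethical approval)** says "Patients who will present with SAE that will be related to the study drugs will be stopped from taking the study drugs".
- **Section 2.15.1 (Ethical issues)** ends, after a paragraph on confidentiality, with "If bleeding occurs, study drug will be stopped and immediate clinical assessment will be undertaken".

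Section 2.8.1.3 adds "There will be no any allowable dose modifications". No section says whether a stop for bleeding is temporary or permanent.

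**The concern.** Section 2.9.6.1 carries the title under which a reader would look for these rules, and it does not agree with the two ethics sections. For a related SAE it gives the investigator a discretion that 2.15.2 removes. For bleeding it has no entry and no pointer to 2.15.1.

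Bleeding is a foreseeable harm in this trial. Section 1.1 names gastrointestinal and, rarely, cerebral bleeding as risks of aspirin, and section 2.11.2 has staff ask about blood in vomit or stools at enrolment and at follow-up visits. The protocol therefore looks for these events but does not state the consequence in one place.

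The first stake is patient safety. The second is data consistency: section 2.7 lists adverse events and compliance to study medication as secondary outcomes. Compliance is a monthly pill count averaged over months (section 2.8.3), so differences in when the drug is stopped can carry into exposure, compliance and discontinuation data.

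**Working it through.** No arithmetic applies. The check is to set the sections side by side, event by event.

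| Event | Sections 2.15.1 and 2.15.2 | Section 2.9.6.1 | Result |
|---|---|---|---|
| SAE related to study drug | Stop is mandatory (2.15.2) | Listed, at the investigator's discretion | Direct contradiction on whether there is discretion |
| Bleed that is a related SAE | Stop is mandatory (2.15.1 and 2.15.2) | Reached through the related-SAE item, discretionary | Same contradiction |
| Bleed that amounts to an exclusion condition | Stop is mandatory (2.15.1) | Reached through the exclusion-criteria item, discretionary | Mandatory against discretionary, by an indirect route |
| Any other bleed | Stop is mandatory (2.15.1) | No entry | Omission |

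**Step 1: do the sections describe the same act for a related SAE?** Yes. Section 2.9.6.1 speaks of withdrawal from study treatment procedures and keeps withdrawn patients in follow-up to six months, so it is not only about leaving the study. Section 2.15.2 speaks of being stopped from taking the study drugs. Same event, same act, different force.

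**Step 2: how far does the exclusion-criteria item reach for bleeding?** The nearest entries in section 2.9.2.2 are "Predisposition to bleeding", which is a tendency and not an event, and peptic ulcer disease. The eligibility form in Appendix 2 asks "Does the participant have active or history of peptic ulceration or gastrointestinal bleeding within the last year", which adds gastrointestinal bleeding only. A non-serious nosebleed in a patient with no bleeding disorder falls under 2.15.1 and meets none of the four reasons in 2.9.6.1.

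**Step 3: is there a cross-reference?** No. Section 2.9.6.1 does not point to 2.15.1 or 2.15.2, and neither of those points back.

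**Step 4: does the gap reach the comparison by arm?** Randomization is 1:1 and separate at each site (2.9.3), the research team is blinded (2.9.4), analysis is by intention to treat (2.13.2 and 2.13.3), and withdrawn patients continue in follow-up (2.9.6.1 and 2.9.6.2). If one site stops the drug more readily than the other, blinded staff apply that practice to both arms. The amount of treatment received may vary with local reading, but the randomized comparison stands.

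**The case against.** The best defence is that a careful site can satisfy every section at once. If it stops the drug for any bleed and for any related SAE, it complies with 2.15.1 and 2.15.2 and does nothing that 2.9.6.1 forbids. A site that continued the drug would breach an ethics section. On this view the risk is an overlooked clause, not two compliant courses of action. The protocol does not say that staff will work from 2.9.6.1 alone, and it provides for training on the protocol (2.16). Section 2.15.1 may also describe an immediate stop pending assessment, which need not be the withdrawal meant in 2.9.6.1.

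Much of this stands for bleeding. A reader might infer that the bleeding rules contradict each other outright. They do not: 2.9.6.1 is silent on bleeding, does not say the drug continues, and does not call its list exhaustive. That part is an omission and a missing cross-reference. The possibility of a temporary stop does not settle the matter, since no section says which kind of stop is meant.

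The defence is weaker for the related SAE. The same event is listed in both places, and a stated discretion cannot sit beside a stated obligation.

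A reader might also infer that bleeds cannot be recorded as a reason for stopping. The documents do not support that. The off-study form in Appendix 3 has an adverse-event reason and a comments field, and the adverse-event log on the same case report form takes dates, relationship, grade and seriousness for each event.

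**Conclusion.** The point holds in two parts of unequal strength. For a drug-related SAE, sections 2.15.2 and 2.9.6.1 contradict each other: mandatory against discretionary. For bleeding, 2.15.1 sets an unqualified mandatory stop that the withdrawal list neither names nor refers to, and that list's indirect routes are discretionary and incomplete.

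The consequence is that these events may be handled inconsistently by anyone who relies on 2.9.6.1 alone, with effects on patient safety and on the consistency of exposure, compliance and discontinuation data. That someone would do so is an inference from the section's title. The size cannot be estimated: the documents give no expected rate of bleeding or of related SAEs, and the conclusion does not depend on one.

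A reader might go further and conclude that discontinuation counts by arm cannot be interpreted. The documents do not support that, given randomization within site, blinded staff, intention-to-treat analysis and continued follow-up. These are also rules for individual patients; nothing here concerns stopping the trial.

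**What to change.** Reconcile sections 2.9.6.1, 2.15.1 and 2.15.2 into one rule set, placed in 2.9.6.1. For each event it should state whether stopping is mandatory or discretionary. For bleeding it should state which bleeds are covered and whether the stop is temporary or permanent. Sections 2.15.1 and 2.15.2 should then refer to it instead of restating it. Which rule applies is a clinical decision for the investigators.

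A separate bleeding code on the off-study form would make tabulation easier but is optional.

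The same edit could pick up two neighbouring mismatches, which are separate from this point. Section 2.8.4 makes withdrawal mandatory when antiplatelets, anticoagulants or methotrexate become essential, while 2.9.6.1 makes it discretionary for a prohibited medication. Section 2.15.2 follows patients stopped for a related SAE to 12 months, while 2.9.6.1 follows withdrawn patients to six.

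The cost is protocol wording and its submission as an amendment under 2.15.3. Sample size, visits and analysis do not change.

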### **2.15.2 Ethical approval**

The study will be conducted according to ICH GCP guidelines and the Declaration of Helsinki (Version 2008), and it is the responsibility of the Investigators to ensure adherence. The investigator will ensure all personnel involved in the study are already trained for Good Clinical Practice (GCP) and/or Good Clinical and Laboratory Practice (GCLP). Study personnel will also be trained on standard operating procedures (SOPs) that are related to the protocol and will follow the GCP and GCLP guidelines.

Patients who will present with SAE that will be related to the study drugs will be stopped from taking the study drugs and referred to the study clinician for management. These patients will then be followed up to complete the 12 months of follow up.

This protocol will be submitted concurrently to the institutional ethical committees of the Muhimbili University of Health and Allied Sciences (MUHAS) and the National Health Research Ethics Committee at the National Institute of Medical Research (NIMR) for ethical approval. Letters of protocol approval by the ethical committees will have to be obtained prior to the commencement of the study, as well as approval for other study documents subject to ethical committees' review. Approval of the protocol and the study drugs will be done by the Tanzania Medicine and Medical Devices Authority (TMDA).

The Investigator and the Supervisors will also be responsible for informing the ethics committees of any SAEs as required, and submitting six monthly report as required. No study materials will be obtained from study participants before approval from the relevant bodies.

The investigator and statistician will be responsible for data analysis. Staff will also be responsible for coordinating the response to any SAE's that arise during the course of the trial and reporting these if indicated to the investigator, who will then report to the appropriate board/committee. Continuous study monitoring will be performed by the investigator in collaboration with an internal monitor who will closely follow up and review study progress, adverse events, any protocol deviations, laboratory data and clinical information. The data and safety monitoring board (DSMB) will also independently monitor the study at intervals to review progress reports, safety data, trial performance and progress and make pertinent recommendations to research ethics committees, regulatory authority, directorate of research and publications at MUHAS and the investigator. The DSMB will comprise of a clinical pharmacologist, a physician and a biostatistician. The DSMB will hold scheduled meetings prior to commencement of data

collection, at 3 months after data collection has started and at the end of the study. These meetings will be headed by the clinical pharmacologist who will be the chairperson of the DSMB.

### **2.15.3 Modifications of the protocol**

This study will be conducted in compliance with the current version of the protocol. Any change to the protocol document or Informed Consent Form that affects the scientific intent, study design, patient safety, or may affect a participant's willingness to continue participation in the study will be considered an amendment, and therefore will be written and filed as an amendment to this protocol and/or informed consent form. All such amendments will be submitted to the ethical committees, for approval prior to becoming effective

### **2.15.4 Protocol Deviations**

All protocol deviations will have to be recorded in the patient record on the CRF and will have to be reported to the investigator. Protocol deviations will be assessed for significance by the investigator. Those deviations that will be deemed to have a potential impact on the integrity of the study results, patient safety or the ethical acceptability of the trial will be reported to the ethical committees. Where deviations to the protocol will identify issues for protocol review, the protocol will be amended.

### **2.15.5 Participant Reimbursement**

Eight thousand Tanzanian shillings (8000 Tshs) will be given to every participant to cover for transport cost and lunch whenever a patient will have to come for follow up visits other than his/her routine care schedule.

### **2.15.6 Study Insurance**

The investigator will purchase an insurance coverage from the National Insurance Corporation for the proposed study. This insurance will be payable at an event of death of the life insured and/ or total permanent disability resulting from the study drugs but not from any other cause which has nothing to do with the study.

## **2.16 Study limitations and mitigation measures**

Adherence to both ARV drugs and ASA measured by pill count may not be fully objective as patients may throw away their pills or forget to return with their study drug boxes and bottles to

the follow up visits. To ensure that adherence by pill count, which will be used in the proposed study, reflects the nearly true adherence, both at consenting and throughout the study, the participants will be reminded by a text message a day before clinic visit to carry their drug boxes and bottles with them on the visit day. The participants will also be educated on the importance of complying with the study procedure including adherently taking their study drugs and faithfully returning their study drug boxes and bottles for pill count. Ideally, measuring drug levels would be the most appropriate method of assessing adherence. However, the method is very costly and cannot be accommodated within the available limited budget.

Since some of the laboratory results will rely on the information available in the clinic records, some laboratory results may be missing. Special efforts will be made to emphasize the importance of performing the follow up laboratory tests as recommended in the care and treatment guideline. Such efforts include

- The research team will be properly trained on the protocol with the emphasis on time points where blood samples must be routinely collected (to ensure that they are collected) and recorded for the study
- There will also be flow charts in the blood sample collection rooms showing time points to collect samples
- Posters will also be put on the tables of the study doctors indicating when these investigations should be done

## **2.17 Dissemination plan**

The study findings will be disseminated by:

- Publications in peer review journals
- Presentation at International, regional and local scientific conferences
- Public defense of the thesis at University level
- Presentation of the study reports to the MoHCDGEC/policy makers, the National Aids Control Programme, NIMR etc.
- Official meeting with the study participants.

### 3. BUDGET AND ITS JUSTIFICATION

#### 3.1 Budget

| Category                | Item Description       | Specification | Quantity per                                   | Quantity           | Unit cost(Tshs) Per item                       | Total cost(Tshs)     |
|-------------------------|------------------------|---------------|------------------------------------------------|--------------------|------------------------------------------------|----------------------|
|                         |                        | Tests  | kits                                    | sample size |                                                |                      |
| Laboratory tests | HIV Viral load         | 3             |                                                | 908                | 45,000.00                                      | 40,860,000.00        |
|                         | CD4 count              | 2             |                                                | 908                | 15,000.00                                      | 13,620,000.00        |
|                         | Lipid profile          | 2             |                                                | 908                | 6,400.00                                       | 5,811,200.00         |
|                         | sCD14                  | 3             | 8                                              | 1362               | -                                              | -                    |
|                         | sP- selectin           | 3             | 15                                             | 1362               | -                                              | -                    |
|                         | UPT                    | 2722          | 23                                             | 303                | 12,000.00                                      | 276,000.00           |
|                         | FBP                    | 2             |                                                | 908                | 16,000.00                                      | 14,528,000.00        |
|                         | RFT                    | 2             |                                                | 908                | 2,860.00                                       | 2,596,880.00         |
|                         | LFT                    | 2             |                                                | 908                | 3,280.00                                       | 2,978,240.00         |
|                         | Sub Total       |               |                                                |                    |                                                | 80,670,320.00 |
|                         |                        |               |                                                |                    |                                                |                      |
| Equipment        | BP machine             |               |                                                | 2                  | 150,000.00                                     | 300,000.00           |
|                         | Sub Total       |               |                                                |                    |                                                | 300,000.00    |
|                         |                        | Tablet | days                                    | sample size |                                                |                      |
| Study drugs      | Placebo                | 100000        | 183                                            | 227                | 81.00                                          | 8,100,000.00         |
|                         | 75 mg ASA              | 50000         | 183                                            | 227                | 81.00                                          | 4,050,000.00         |
|                         | Sub Total       |               |                                                |                    |                                                | 12,150,000.00 |
|                         |                        |               |                                                |                    |                                                |                      |
|                         |                        | staff  | remuneration per patient for each staff | visits      | remuneration per 6 months for all staff |                      |
| Personnel        | Pharmacists            | 2             | 500.00                                         | 7                  | 1,589,000.00                                   | 1,589,000.00         |
|                         | Prescreening nurse     | 2             | 500.00                                         | 7                  | 1,589,000.00                                   | 1,589,000.00         |
|                         | Phlebotomy nurse       | 2             | 500.00                                         | 7                  | 1,589,000.00                                   | 1,589,000.00         |
|                         | Informed consent nurse | 2             | 1,000.00                                       | 7                  | 3,178,000.00                                   | 3,178,000.00         |
|                         | Doctor                 | 2             | 1,000.00                                       | 7                  | 3,178,000.00                                   | 3,178,000.00         |
|                         | Investigator           | 1             | N/A                                            | N/A                | 1,800,000.00                                   | 1,800,000.00         |

|                    |                                        |     |               |                    |              |                       |
|--------------------|----------------------------------------|-----|---------------|--------------------|--------------|-----------------------|
|                    | Sub Total                       |     |               |                    |              | 12,923,000.00  |
|                    |                                        |     |               |                    |              |                       |
|                    |                                        |     | visits | sample size |              |                       |
| Direct Cost | Ethical clearance (NIMR)               |     |               |                    | 1,100,000.00 | 1,100,000.00          |
|                    | Ethical clearance (MUHAS)              |     |               |                    | 1,000,000.00 | 1,000,000.00          |
|                    | Ethical clearance (TMDA)               |     |               |                    | -            | -                     |
|                    | Clinical trial participation insurance | 454 | 7             | 454                | 12,841.60    | 5,830,086.40          |
|                    | Voucher for telephone tracing          |     |               |                    | 309,545.00   | 309,545.00            |
|                    | Sample transport                       |     |               |                    | 4,952,730.00 | 4,952,730.00          |
|                    | Stationeries                           |     |               |                    | 854,345.00   | 854,345.00            |
|                    | Public transport fare and lunch        | 454 | 1             | 454                | 8,000.00     | 3,632,000.00          |
|                    |                                        |     |               |                    |              | 17,678,706.40  |
|                    |                                        |     |               |                    |              |                       |
|                    | TOTAL BUDGET                    |     |               |                    |              | 123,722,026.40 |

